##### Follow-up visits

The first follow-up visit will be after two weeks of the randomization to check for safety and tolerability of the treatment initiated. There will be visits at week 6, 10, 14, 18 and 22. On all these visits the patients will collect their trial treatment from their treatment centers. The study drugs at the two sites will be dispensed from the local pharmacy departments. The research assistants will collect and deliver these to the patient at a previously agreed upon location. This will give the opportunity for the research team to closely monitor the patient’s physical and mental health, side effects and compliance (by pill count).

Female patients with childbearing capacity taking part in the clinical trial will have a pregnancy test on a regular basis. If they should become pregnant during the course of the study, they will be withdrawn from the study.

During the course of the study the patient’s individual consultant and mental health care team will be responsible for their overall care. If any concerns do occur with regard to the research study, the research team can be contacted to discuss these concerns 24 h a day 7 days per week. The patient will have their study card with the telephone number of the research clinicians and clinical trial office if they have any concerns or questions.

One of the co-investigators and/or the study doctor will be available 24 h per day 7 days per week and will be contacted by the patient or carers or the research clinicians should this be necessary.

#### 26 week, final visit

At this visit all clinical, neuropsychological, physical and hematological assessments will be completed. Trial medication will cease.

At all visits the patient’s cumulative clinical drug treatment will be updated from the case notes.

#### Study coordination

The study will be coordinated by weekly meetings by local investigators. There will be two weekly tele- or video-conferences with the chief investigator. We are also able to use the access grid facility at the University of Manchester.

#### Patient safety

The patients’ day-to-day care is the responsibility of the consultant in charge of the patient. Any study related safety concerns are the responsibility of the local principal investigators (P.I.). The P.I.s and the co-investigators can be contacted at any time via the clinical trials office or/and through the senior research clinicians.

#### Patient withdrawal

Patients may be withdrawn from the treatment study for the following reasons:

1. At their own request.

2. At the discretion of the investigator.

3. If any patients suffers a serious adverse event, or moderate to severe adverse drug reaction.

4. Any patients meet the criteria for insufficient compliance. This is defined as either taking less than 75% of antipsychotic or trial medication between assessment points at baseline, 14 and 26 weeks; or missing trial medications or antipsychotic altogether for seven days or more at any period.

5. If a patient becomes pregnant.

They may withdraw from the study entirely (that is, follow-up) at their own request or at the investigator’s discretion.

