All analyses will be based, as far as possible, on the intention-to-treat principle (with weighting adjustments to allow for differential loss to follow-up – see below). Analysis of the three- and six-month quantitative outcomes will be based on an analysis of covariance (ANCOVA), using relevant baseline score and center membership as covariates. In line with the factorial design, we will initially evaluate the interaction between ondansetron and simvastatin. If this (as expected) is not statistically-significant, we will proceed to estimate the main effects of each of these two drugs separately (that is, in terms of the 2 × 2 design in the table above, by comparison of row means for ondansetron and column means for simvastatin, respectively). If the interaction was found to be statistically-significant the analysis would involve the estimation of all of the parameters of the saturated model. Patterns of missing outcome data will be examined as a function of recorded baseline characteristics and patterns of compliance with the treatment protocol. Adjustments will be made to allow for biases arising from patterns of missing outcome data linked to protocol violations using inverse-probability weighting.

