### Safety assessments

#### Medical history

The primary purpose of screening is to check for inclusion and exclusion criteria. The RAs will arrange for a doctor to complete checklists for medical history, review of systems, a physical exam and arrange a blood draw for hematology and differential white cell count, and for clinical chemistry to confirm normal renal and liver function. These assessments will be repeated after six months in the trial or at the time of withdrawal from the study.

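### The protocol lets the investigator end a randomised patient's follow-up without criteria, and two sections disagree on what pregnancy ends

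*Protocol article*

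**What the plan says.** The Patient withdrawal section has two tiers.

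- **Leaving treatment.** The list opens "Patients may be withdrawn from the treatment study for the following reasons" and gives five: own request, investigator discretion, a serious adverse event or a moderate to severe adverse drug reaction, insufficient compliance, and pregnancy.
- **Leaving follow-up.** A separate sentence then says "They may withdraw from the study entirely (that is, follow-up) at their own request or at the investigator’s discretion". Nothing limits or defines the investigator's discretion.

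The Follow-up visits section treats pregnancy differently: "If they should become pregnant during the course of the study, they will be withdrawn from the study".

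On analysis, Power calculation and statistical analysis says "All analyses will be based, as far as possible, on the intention-to-treat principle", with weighting for differential loss to follow-up. It continues: "Patterns of missing outcome data will be examined as a function of recorded baseline characteristics and patterns of compliance with the treatment protocol". The remedy is then named: "Adjustments will be made to allow for biases arising from patterns of missing outcome data linked to protocol violations using inverse-probability weighting".

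The schedule of assessments (Table 3) has PANSS at randomization and at all seven follow-up visits to week 26. Withdrawal criteria are checked at randomization and at each visit to week 22.

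**The concern.** An intention-to-treat comparison needs the outcome of every randomised patient, including those who stop the trial drug. Separating the two kinds of withdrawal is the right start. The next step undoes part of it, because someone other than the patient may end outcome collection for any reason.

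An investigator is most likely to use that discretion when a patient is doing badly, tolerating treatment poorly or proving hard to manage. These are post-randomisation events, and they can differ between cells if either drug affects symptoms or tolerability. Blinding keeps knowledge of the allocation out of the decision but does not keep out the drug's effects. At stake are primary-outcome ratings that could have been obtained at visits already scheduled, and that a model must replace once they are lost.

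**Working it through.** **1. The withdrawal rules side by side**

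- Adverse event or reaction, and insufficient compliance: permissive, and listed for leaving treatment only.
- Pregnancy: permissive and for treatment in Patient withdrawal; mandatory and from the study in Follow-up visits. A site cannot tell from these whether outcome ratings continue.
- Investigator discretion: listed for treatment, and again for follow-up, with no criteria in either place.

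So one route out of follow-up is open-ended and not the patient's choice, and for one event the two sections disagree.

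**2. Does the planned weighting cover it?**

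Inverse-probability weighting removes bias when, given the variables in the weight model, missingness does not depend on the unseen outcome. The protocol names baseline characteristics and compliance. It does not name symptom course or tolerability after randomisation. PANSS and side effects are recorded at each visit, so they could be added to the model. Even then, a decision based on something the investigator saw but did not record would stay outside it.

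**3. Size**

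Inputs from Power calculation and statistical analysis: 54 per cell, 20% dropout, SD 5, a 2-point difference for a single drug, and alpha 0.05 (taken as two-sided; the text does not say).

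- The plan's own figure: 54 × (1 − 0.20) = 43.2, so 43 per cell. This reproduces. The total expected loss is 216 − 4 × 43 = 44 outcomes.
- That loss is from all causes. No figure in the document splits it by reason, so the number due to investigator-ended follow-up or pregnancy cannot be derived.
- An outer limit on precision: with power = Φ(2 / (5√(2/n)) − 1.96) for a 2-point main effect, n = 86 per margin gives 2/0.762 − 1.96 = 0.66, or 75%. With no loss, n = 108 gives 2/0.680 − 1.96 = 0.98, or 84%. Within the expected dropout, the rules at issue cannot account for more than this gap, and probably account for a small part of it. (The protocol states over 90% at 86 per margin. That discrepancy is a separate matter.)
- Bias, on assumed inputs: if one arm of the contrast loses an extra fraction f of its patients, whose scores are m points worse than those of completers, the observed-case difference shifts by f × m.
  - f = 0.10 and m = 3 to 5: 0.3 to 0.5 points, which is 0.3/2 = 15% to 0.5/2 = 25% of the planned 2-point difference.
  - Wider range, f = 0.05 to 0.20 and m = 2 to 5: 0.1 to 1.0 points.
  - Neither f nor m comes from the documents. These are unweighted figures; weighting would remove some, all or none of the shift, depending on step 2.

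**The case against.** The strongest reply is that the protocol already does most of what is asked. It separates treatment from follow-up, its language is permissive, it qualifies intention-to-treat, and it foresees differential loss and plans for it. It is also a condensed article, so the detail of visits after stopping treatment may sit in the full protocol.

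Much of this stands, and it rules out several stronger readings that a reader might infer:

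- **That adverse reactions or poor compliance cost outcome data by rule.** They do not. The compliance item, "Any patients meet the criteria for insufficient compliance", and the adverse-event item are permissive and concern treatment only. Pregnancy is the only event with mandatory withdrawal from the study.
- **That the plan claims full intention-to-treat and contradicts it.** The claim is qualified, and weighting accompanies it.
- **That an exit assessment replaces the week-26 rating.** The sentence under Medical history, "These assessments will be repeated after six months in the trial or at the time of withdrawal from the study", refers to history, physical examination and safety bloods, not PANSS.
- **That the 44 expected losses, or a definite gain in power, belong to this clause.** The 20% comes from a previous trial and the pilot and covers every cause.

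Two things are not answered. The discretion to end follow-up is written text, not detail left out of an article. And planning to weight for loss does not justify a rule that permits avoidable loss.

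**Conclusion.** The point holds in limited form. The protocol permits avoidable missing week-26 PANSS scores through an unrestricted investigator decision, and it is inconsistent on whether pregnancy ends treatment or the whole study. Such losses may depend on symptom course or tolerability, and weighting as described may not correct for them.

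The size is unknown. It depends on how often the discretion is used and on whether that use differs by arm, and the documents give neither. The bias figures above show only what would follow under the assumed inputs. This is a cheap improvement, not a flaw that invalidates the design.

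**What to change.** Amend Patient withdrawal and Follow-up visits as follows:

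1. State that stopping trial medication for any of the listed reasons does not by itself end outcome assessment.
2. State that PANSS is still rated at the scheduled visits to week 26 unless the patient withdraws consent or can no longer take part in assessments, with the reason recorded.
3. Remove the unrestricted investigator discretion to end follow-up. The provision for a patient who can no longer be assessed, including one who loses competence, covers the legitimate need for judgement.
4. Reconcile the pregnancy wording in the two sections so that it is clear whether outcome follow-up continues.

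The reasons for stopping medication stay as they are, and no clinical rule is proposed. The cost is a short amendment, an instruction to both sites, and some extra ratings of patients who are off medication, at visits already in Table 3. Weighting remains for the losses that cannot be avoided.

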### Ethical and regulatory standards

#### Local Research Ethics Committee (LREC)

Ethical approval covering all sites was obtained from the research and ethics committee of the Pakistan Institute of Learning and Living and was submitted to the funding body, Stanley Medical Research Institute.

#### Data and Safety Monitoring Board (DSMB)

The DSMB will be constituted according to NIH guidelines, for oversight and monitoring of the conduct of clinical trial. DSMB will meet every six months to ensure the safety of participants and the validity and integrity of the data.

#### Declaration of Helsinki

The research study will be performed in accordance with the guidelines in the Declaration of Helsinki (1974) as revised in Tokyo (1975), Venice (1983), Hong Kong (1989), South Africa (1996) and Scotland (2000).

All members of the research team will comply with International Conference on Harmonisation/Good Clinical Practice (ICH/GCP) Guidelines (1996) which are consistent with principles which have their origin in the Declaration of Helsinki.

## Discussion

Schizophrenia is characterized by disorder of thought, perception, volition, socialization and psychomotor behavior. During the clinical course of the illness, deterioration is manifested with increased severity and persistence of negative and positive symptoms. Standard pharmacological treatments have little impact on negative symptoms leading to diminished social and functional outcome. Anti-inflammatory treatments have been shown to have some beneficial effects in schizophrenia. Both simvastatin and ondansetron provide some evidence of a reduction in symptoms compared to treatment as usual.

The preliminary feasibility study adding ondansetron or simvastatin to TAU in patients with chronic schizophrenia (ClinicalTrails.gov NCT00929955) showed both treatments were well tolerated and no serious side effects were reported. Findings are from this randomized controlled trial of simvastatin and ondansetron added to TAU may contribute to evidence in the management of negative symptoms and cognitive deficits in patients with schizophrenia.

## Trial status

The study is active and currently recruiting patients. We anticipate completing recruitment by the end of 2012 and final assessments completed by June 2013 (Table 4).

**Table 4 T4:** Timeline

**Milestones (months)**	**–3**	**1**	**3**	**4**	**5**	**6**	**10**	**16**	**24**	**28**	**30**	**32**	**34**	**36**
Setting up/ethical approval	X	X	X											
Staff recruitment/training		X	X	X										
Patient recruitment/11 per month				X	X	X	X	X	X					
Intervention				X	X	X	X	X	X	X	X			
Data entry				X	X	X	X	X	X	X	X	X		
Write up and analysis											X	X	X	X

## Abbreviations

AE: Adverse Events; ANCOVA: Analysis of Covariance; BMI: Body Mass Index; BNF: British National Formulary; BP: Blood Pressure; CANTAB: Cambridge Neuropsychological Test Automated Battery; CGI: Clinical Global Impression; CRP: C-reactive protein; CSF: cerebrospinal fluid; DSMB: Data and Safety Monitoring Board; DSM-IV TR: Diagnostic and Statistical Manual-IV; ECG: Electro Cardio Gram; GAF: Global Assessment of Functioing; GCP: Good Clinical Practice; ICD-10: International Statiscal Classification of Diseases and Related Health Problems; ICH: International Conference for Harmonisation; IED: Intra-extra Dimensional Set Shift; HR: Heart Rate; LREC: Local Research Ethics Committee; MATRICS: Measurement and Treatment Research to Improve Cognition in Schizophrenia; MDT: Multi-Disciplinary Teams; MRC: Medical Research Council; NIMH: National Institute of Mental Health; OD: Once Daily; PANSS: Postive and Negative Syndrome Scale; Pt.: Patient; PI: Prinicipal Investigator; QLS: Quaility of Life Scale; QOL: Quality of Life; RA: Research Assisstants; RMO: Resident Medical officer; SFS: Socal Functioing Scale; SCID: Structured Clinical Interview for DSM-IV; SMRI: Stanley Medical Research Institute; SWM: Spatial Working memory; PAL: Paired Associates Learning; TAU: Treatment As Usual; WAIS: Wechsler Adult Intelligence Scale; W2: Week2; W6: Week 6; W10: Week10; W14: Week14; W18: Week18; W22: Week22; W26: Week26.
